## Abstract

**Background:**

The 4th Industrial Revolution with the advent of the smart era, in which artificial intelligence, such as big data analysis and machine learning, is expected, and the provision of healthcare services using smartphones has become a reality. In particular, high-risk mothers who experience gestational diabetes, gestational hypertension, and prenatal and postpartum depression are highly likely to have adverse effects on the mother and newborn due to the disease. Therefore, continuous observation and intervention in health management are needed to prevent diseases and promote healthy behavior for a healthy life.

**Methods:**

This randomized controlled trial will provide mothers 18 years of age or older with health care information collected based on evidence-based literature data using a smartphone app for 6 weeks. About 500 mothers will be selected in consideration of the dropout rate due to the characteristics of mothers. The study group and control group will be computer-generated in a 1:1 ratio through random assignment. The research group will receive health management items through the app, and health management information suitable for the pregnancy cycle is pushed to an alarm. The control group will receive the health management information of the paper. We also followed the procedure for developing mobile apps using the IDEAS framework.

**Discussion:**

These results show the effectiveness of smart medical healthcare services and promote changes in health behaviors throughout pregnancy in high-risk mothers.

**Trial registration:**

Clinical trial registration information for this study has been registered with WHO ICTRP and CRIS (Korea Clinical Research Information Service, CRIS). Clinical trial registration information is as follows:

Study of development of integrated smart health management service for the whole life cycle of high-risk mothers and newborns based on community, KCT0007193. Registered on April 14, 2022, prospectively registered. This protocol version is Version 1.0. April 14, 2022.

## Background

High-risk mothers refer to those who are more likely to have adverse effects on their newborns than normal mothers [1]. They can have a fatal impact on both mothers and newborns because of gestational diabetes, gestational hypertension, and depression during pregnancy. In recent years, medical interventions during pregnancy have shown healthy outcomes for childbirth, mothers, and newborns. Several protocols for high-risk mothers and newborns have been developed abroad through a comparison of normal and high-risk mothers [2]. In the USA, a lifestyle management program is in operation for high-risk mothers with gestational diabetes, and provided guidance and online presentation of lifestyle coaches, modules on diet and exercise management to help women give birth, and information on health and neonatal [3]. In addition, a protocol for collecting maternal healthcare data that can predict and identify patterns of high-risk mothers is also provided; thus, a mother can predict whether she is considered a high-risk mother to prevent any disease progression [4, 5]. In the Netherlands, the Smarter Pregnancy app is provided to prevent pregnancy complications and to manage the health of newborns and mothers [6]. It monitors pregnant women’s questionnaires, blood tests, and physical activity every 18 and 24 weeks, and helps pregnant women manage their hospital appointments and medication adherence. In addition, in Australia, programs and coaching for intervention management of high-risk mothers’ lifestyles, dietary habits, and drinking are provided under the name of “Get Health in Pregnancy,” and it has been confirmed that they manage their mothers through a continuous contact network [7].

However, cognitive-behavioral intervention [8], a psychological theory of behavior, reports that it is important to be able to control and regulate one’s behavior to change it [9, 10]. Based on this, to promote changes to healthy behaviors through psychology and preventive aspects, we propose a behavior change technology [11] that aims for healthy behaviors and provides healthy lifestyle interventions to produce positive results. Therefore, for mothers who need a healthy lifestyle and healthy behavior, services that can provide these are necessary. Studies about using the app, which mediates diet and physical activity of mothers who are overweight and with obesity, were reported to have changes in health behavior [12]. Despite the protocols and healthcare services currently being mediated in many countries to promote healthy behavior for mothers, the fatality rate is high; thus, providing healthcare services for the entire life cycle of high-risk mothers who need more intensive care is important. We believe that the number of protocols used is insignificant [13]. Therefore, providing healthcare services to high-risk mothers throughout the entire pregnancy cycle is vital for a healthier behavior, reducing the maternal mortality rate, the incidence of complications in high-risk mothers and newborns, and improving the survival rate. It is expected to be the most powerful preventive measure against low fertility. Although the health management information protocol is expected to be quite effective for high-risk pregnant mothers, we currently lack the means to solve this problem. Therefore, it is impossible to link the treatments for high-risk mothers and newborns. In addition, as non-face-to-face personal health management culture using ICT is spreading due to COVID-19 with an increasing interest in personal health information, preventive measures, and collection of medical data of high-risk mothers, newborns, and women of childbearing [14] are necessary to improve the quality of life and alleviate the burden of medical expenses through a regular health management system using digital technology.

On the other hand, a smartphone provided by the health management system has recently been attracting attention. Smartphones or mobile phones are convenient and accessible and suitable to present age when the demand for PHRs and smart medical technology are important [15], enabling various opportunities for health care. In addition, the use of the latest mobile technologies called mobile health or mHealth is increasing in popularity in the medical field, which has become an important advancement [16]. Therefore, high-risk mothers are the most suitable target group for applying mHealth because of its optimal functions.

We believe that health management information service protocols in the entire pregnancy of high-risk mothers are important; thus, we propose the development of a health application protocol through a smartphone to promote better health behavior.

## Methods/design

### Objectives

The overall goal of this trial is to target the effectiveness of a smartphone app for health care interventions in high-risk mothers. Providing healthcare interventions via a smartphone app demonstrates the effectiveness of smart medical technology. Therefore, in this study, more specifically, the study group using the app and the group using paper health management information will compare over a period of 6 weeks.

### Study design

This study will be conducted in accordance with SPIRIT’s clinical trial protocol guidelines. This study will be conducted as a clinical trial study according to the following framework and will compare the two groups. This randomized controlled trial (two-armed RCT) will be conducted for 6 weeks to provide healthcare service information based on a smartphone app for high-risk mothers during their entire pregnancy. A diagram of the study design is shown in Fig. 1. In addition, based on the research design, the procedure for developing a mobile app using the IDEAS framework [17] was followed, which is an appropriate procedure to lead to healthy and positive outcomes through the development of mobile digital medical interventions. The procedure is as follows [18] (Table 1):

**Fig. 1 Fig1:**
[figure not shown]
Trial flow diagram

**Table 1 Tab1:** List of 10 phases of the IDEAS framework

1	Empathize with target users
2	Specify target behavior
3	Ground in behavioral theory
4	Ideate implementation strategies
5	Prototype potential products
6	Gather user feedback
7	Build a minimum viable product
8	Pilot test to assess potential efficacy and usability
9	Evaluate efficacy in randomized controlled trial
10	Share intervention and findings

### Ethics

This study is in accordance with the WMA Declaration of Helsinki—Ethical Principles for Medical Research Involving Human Subjects. Also, this study received institutional ethics approval from the Gachon University Gil Hospital in South Korea in January 2022.

### Enrollment and eligibility

This study will be conducted at the Department of Obstetrics and Gynecology and Public Medical Center of Gachon University Gil Hospital in South Korea. This hospital is affiliated with the university and is in charge of medical care for the entire pregnancy cycle. Women aged ≥ 18 years who were diagnosed with gestational diabetes, gestational hypertension, and depression during or after pregnancy will recruit if they own a smartphone.

Participants selected by the medical staff will be admitted to the hospital. After that, you will be informed of consent and explanation for participation in the study by the research staff. Written or verbal informed consent will be obtained from all participants. Personal and demographic information, including contact information, will be collected. Also, On the consent form, participants will be asked if they agree to use of their data should they choose to withdraw from the trial. Participants will also be asked for permission for the research team to share relevant data with people from the Universities taking part in the research or from regulatory authorities, where relevant. This trial does not involve collecting biological specimens for storage. Upon randomization, participants will be categorized into two groups (intervention and control groups). Next, all participants will receive a Bluetooth weighing machine, blood pressure machine, and wearable blood glucose machine.

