### Allocation of participants

The participants will be randomly assigned in the intervention group applying the app and the general control group providing the paper guidelines performed using computer-generated assignments in a 1:1 ratio. Considering the characteristics of the intervention, both the participants and researchers will aware of the group to which they will be assigned. In addition, this study will be conducted as a stratified block. Accordingly, the registration of participants and the assignment of interventions will be performed by the medical staff, and a random number table will be generated through a computer program to assign and enroll participants in the study.

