### Intervention channel: smartphone app

Mothers randomly assigned to the intervention group will download the app. It will be available free of charge on Android-based and Google Play. This app fills in one’s gestational age, expected delivery date, basic information about the disease, exercise amount, and dietary pattern during registration. By pushing a message through this app, one can acquire health information and promote one’s own health behavior. The study participants will be received a message programmed to push notifications every day. The items configured in Table 2 were pushed as messages according to the pregnancy cycle. Mothers will receive the health information that is needed to check via push notifications or will be viewed by clicking on it.

Additionally, mothers will be required to access and engage the app on a daily basis. In particular, blood pressure, blood sugar, and weight were recorded. These daily records can provide a cautionary warning when risk levels are reached during pregnancy, which can prevent emergencies.

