### Outcome measure

Table 3 shows the intervention and control groups measured item results, and the same items will be measured after the 6-week study participation period. Primary measurements will include weight, blood pressure, blood sugar and health literacy, and physical and obstetric characteristics. In addition, character, exercise and nutritional information on basic demographic characteristics and basic psychological state will be collected. For the primary measurement, the same information will be collected for both the primary and final results for comparison with the final result.

**Table 3 Tab3:** Outcome measure items

1	Weight, blood pressure, blood sugar measurement
2	Health information literacy
3	Physical and obstetric characteristics (including height, weight, gestational age, date of birth, etc.)
4	Basic demographic characteristics (spouse, marital status, economic status, etc.)
5	Basic psychological status (prenatal-postpartum depression questionnaire, high-risk-related trauma questionnaire, anxiety, and psychological state)
6	International Physical Activity and Exercise Questionnaire (IPAQ)
7	Nutrition and Dietary Questionnaire
8	Newborn information data (weight, head circumference, pregnancy method, birth period, etc.) (after 6 weeks/in case of delivery)
9	Questions for high-risk mothers
10	Smartphone app evaluation questionnaire (only intervention group)
11	App usage effect confirmation questionnaire (only intervention group)
12	Self-report (only intervention group)

Items 1 to 9 in Table 3 are for the intervention and control groups measurement. Item 1 measures body weight, blood pressure, and blood sugar daily during the study period. The amount of change from the start to the end of the study will be evaluated. Item 9 is about high-risk mothers and asks them to check for the diseases that apply to them, such as gestational hypertension, gestational diabetes, and prenatal-postpartum depression. This item will be completed at the beginning and end of the study. When the study is over, it will also be checked whether the disease is maintained. This can help with the prevalence and maintenance of healthcare-related diseases.

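### The stated order hands out the weight, blood pressure and glucose devices only after open randomisation, so device-based start values for these change scores come after the woman knows her arm

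*Protocol article*

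**What the plan says.** Under Enrollment and eligibility, the Protocol article describes enrolment in order. Women are admitted and asked for consent, and the one data collection described before the randomisation sentence is this: "Personal and demographic information, including contact information, will be collected". Randomisation follows, and then: "Next, all participants will receive a Bluetooth weighing machine, blood pressure machine, and wearable blood glucose machine".

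Allocation of participants states that "both the participants and researchers will aware of the group to which they will be assigned".

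Outcome measure lists weight, blood pressure and blood sugar among the primary measurements (item 1 of Table 3), to be measured daily while the woman is in the study. For this item, "The amount of change from the start to the end of the study will be evaluated". Statistical analysis repeats the idea with a pre-post comparison from first to final outcome. Neither section says when the start value is taken relative to randomisation.

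On the app side, Intervention channel: smartphone app says that "Mothers randomly assigned to the intervention group will download the app" and that users enter their "exercise amount, and dietary pattern during registration". The last paragraph of Outcome measure compares the mother's recorded eating habits, as well as questionnaires, before and after. It does not say which record supplies the earlier value.

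**The concern.** A baseline is useful because it cannot be affected by the assigned arm. If it is taken after an open allocation, that protection is lost in three ways.

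- **Part of the effect may already be in the start value.** The change score then subtracts some of what the trial wants to measure.
- **Conditions of measurement may differ by arm.** Under Intervention, the devices in the app arm pass values automatically to the app, and the recorded values drive push messages. The app also displays changes and can warn at risk levels. The control arm receives paper guidelines. A first reading taken in these different settings can differ between arms for reasons unrelated to the woman's state at entry.
- **Whether a first reading exists may depend on the arm.** A woman who learns her allocation and then supplies no first reading has no change score. Such losses occur after randomisation and can be unequal between arms.

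An analysis plan cannot repair this later. Change scores and any adjustment for the start value would both inherit the problem.

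**Working it through.** The plan gives no figure to reproduce; the point concerns the order of events. Tracing each measurement through the text gives:

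| Measurement | What the Protocol article states | Position relative to open allocation |
|---|---|---|
| Personal and demographic data | Collected before the randomisation sentence (Enrollment and eligibility) | Before |
| Weight, blood pressure, blood sugar from study devices (item 1) | Devices handed out after randomisation; measured daily during the study | After |
| Exercise and diet entries at app registration | App downloaded by women already assigned to the app arm | After, app arm only |
| Health literacy, psychological status, IPAQ, nutrition questionnaire, disease checklist | Both arms (items 1 to 9 of Table 3); the checklist is completed at the beginning and the end | Not stated |

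Step 1. A study device cannot give a reading before it is handed over. Hand-over follows randomisation, and allocation is open. Any start value from these devices is therefore taken when the woman knows her arm.

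Step 2. No other source is named for the item 1 start value, so the first daily device reading is its natural meaning.

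Step 3. In the app arm, the text does not order app installation or first messages against the first reading. The app may be in use at that point, but this is not stated.

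Step 4. Size. Let f be the share of the 6-week effect already present in the first reading. The change score then recovers (1 − f) of the effect. The documents give no value for f. As an illustration only, assume that the effect builds evenly over 6 × 7 = 42 days:

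- first reading after 1 day: f = 1/42 = 2.4%, so 97.6% is recovered;
- first reading after 7 days: f = 7/42 = 16.7%, so 83.3% is recovered.

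This covers dilution only. An immediate reaction to allocation, or a difference in how the first reading is taken, could push the result either way. Nothing in the documents allows that to be sized.

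**The case against.** The strongest reply is that the enrolment section is a narrative, not an assessment schedule, and that the text leaves room for a baseline before allocation. Outcome measure groups demographic data with the primary measurements and psychological state, and demographic data are collected before randomisation. One enrolment battery is therefore a plausible reading. Weight also appears in item 3 of Table 3 with height and gestational age, so a weight from another source may exist. Women are admitted before consent, so clinic values are possible. Fig. 1 is not shown and may place baseline first. Finally, a first-day reading, particularly of weight, may carry very little effect.

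Much of this stands, and it limits the point. A reader might infer that every change score rests on a post-allocation baseline. The documents do not support that: the questionnaires are separate instruments for both arms, and their first timing is unstated rather than late. A reader might also infer that the app-registration entries serve as the baseline for diet and exercise. The only use the text plainly gives them is tailoring diet content, and physical activity is assessed with IPAQ. The reference to recorded eating habits could be read as the registration entry, which has no counterpart in the control arm, but nothing identifies it as such.

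The reply does not remove the core. None of the possible earlier values is named as the start value, and the order that is written puts the devices after open allocation. If Fig. 1 shows otherwise, the text must be reconciled with it.

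**Conclusion.** The point holds for item 1. Followed as written, the device-based start values for weight, blood pressure and blood sugar are taken after open allocation, and no outcome measurement is placed before it in the text. For the questionnaires the order is simply open, and for diet the source of the earlier record is open too.

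This rests on two assumptions: that the start value is a reading from the study devices, and that the unseen flow diagram does not place a baseline assessment earlier. Because of these, confidence is medium. The bias cannot be quantified from the documents; it may be small if the first reading is taken on the first day, and would grow with delay. It is still more than missing detail: the article itself fixes the sequence, it bears on a primary measurement, and it is easily avoided. The change should be made.

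**What to change.** 1. In Enrollment and eligibility, reorder the visit. After consent and before the allocation is opened, measure weight, blood pressure and glucose with the study devices and complete the Table 3 baseline questionnaires (health literacy, psychological status, IPAQ, nutrition and diet, disease checklist), by the same method in both arms. Then randomise, hand over the devices for home use, and install the app in the intervention arm.
2. In Outcome measure, define the start value as these pre-allocation values.
3. State that entries made at app registration are used only to tailor content and not as baseline, and name the both-arm source for the comparison of eating habits.
4. Check that Fig. 1 shows the same order.

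Cost: a somewhat longer enrolment visit, with staff time for the three measurements and the questionnaires before allocation. A single glucose value at enrolment may not be directly comparable with the later daily readings, so the start and end values need to be defined on the same footing. The Trial status section says that the trial has not started, so no collected data are affected.

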### Allocation of participants

The participants will be randomly assigned in the intervention group applying the app and the general control group providing the paper guidelines performed using computer-generated assignments in a 1:1 ratio. Considering the characteristics of the intervention, both the participants and researchers will aware of the group to which they will be assigned. In addition, this study will be conducted as a stratified block. Accordingly, the registration of participants and the assignment of interventions will be performed by the medical staff, and a random number table will be generated through a computer program to assign and enroll participants in the study.

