### Intervention

We will randomize participants to the intervention installed on the app via their smartphone. Mothers using this app measured their weight, blood sugar, and blood pressure every day, and the Bluetooth wearable device automatically entered the values into the app. Through this measured and recorded information, the patient will send an intervention message by push notification according to all pregnancy cycles. The intervention message will be delivered to check the nutritional information and exercise method according to the numerical value, and the mother acquires health information while checking the content. In addition to providing medical information throughout the pregnancy cycle, mothers will also receive a schedule of tests to be performed during pregnancy. By the time the mothers will give birth, they will have healthcare information about newborn care and postpartum disease prevention. With this information, mothers can take healthy precautions that benefit them throughout pregnancy. Furthermore, these healthy behaviors can help prevent diseases in the postpartum period.

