### Statistical analysis

This study will compare the outcomes between the two groups using IBM SPSS software for statistical analysis. For this purpose, descriptive statistics and correlation analysis of each group are performed, and a paired sample T-TEST of two groups is performed, so that comparative analysis can be performed. In addition, pre-post-group comparison analysis will be conducted, especially for both groups, from the first outcome to the final outcome. Hierarchical and stepwise regression analyzes will be conducted to determine the impact of each item to look at changes in health behavior as the end result.

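### The reason given for open allocation covers mothers and delivery staff, but the statement takes in researchers generally, leaving the analysis of shared outcomes unmasked without justification

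*Protocol article*

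**What the plan says.** Under Allocation of participants, the Protocol article gives the decision and its only reason in one sentence: in view of the nature of the intervention, "both the participants and researchers will aware of the group to which they will be assigned". The same section describes the arms as "the intervention group applying the app and the general control group providing the paper guidelines", and says that "the registration of participants and the assignment of interventions will be performed by the medical staff".

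Under Outcome measure, "Items 1 to 9 in Table 3 are for the intervention and control groups measurement"; items 10 to 12 exist only for the app group. Item 8 is "Newborn information data (weight, head circumference, pregnancy method, birth period, etc"; neither its source nor its collector is stated. The primary measurements include weight, blood pressure, blood sugar, health literacy, and physical and obstetric characteristics. Item 1 is measured every day but is evaluated as a change over the study.

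Under Statistical analysis, "This study will compare the outcomes between the two groups using IBM SPSS software for statistical analysis". The methods named are descriptive statistics, correlations, paired t-tests, pre-post comparisons, and hierarchical and stepwise regression. The section does not say who runs them or whether the arms are coded.

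**The concern.** The sentence is a stated design decision, not a gap in a condensed article. It makes researchers aware of allocation, excepts no role and rests on one reason, which holds for some roles and not for others. A fuller plan that masked the analyst would have to qualify it.

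At stake is the direction of discretionary choices. The Sample size section calls the study exploratory, yet the Objectives section aims at the app's effectiveness, and the Abstract's discussion already speaks of the results as showing it. With that expectation on record, an analyst who knows the arms can, without intending to, settle open questions in the app's favour. Bias from the mothers' own knowledge of their arm cannot be avoided in this design; this part can be reduced.

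**Working it through.** No arithmetic applies. The plan gives no figure on masking, and none of its quantities yields the size of an analyst bias. The check sets the stated reason against each role and then asks where knowing the arm could matter.

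**Does the reason cover the role?**

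| Role | Does app versus paper force knowledge of the arm? |
|---|---|
| Mothers | Yes: they use the app or hold the paper |
| Medical staff who register and assign | Yes, once they assign the intervention |
| Staff who support the app | Yes |
| Whoever collects newborn data (item 8) | Not necessarily; the procedure is not described |
| Whoever analyses items 1 to 9 | No: these items exist in both arms and can carry a coded label |

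**Is a coded analysis feasible?** Items 1 to 9 are common to both groups. Items 10 to 12 reveal the arm, as do the app-usage records mentioned under Intervention channel, but both can be held apart. Of items 1 to 9, item 4 is demographic and not an effect measure; this does not affect feasibility.

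**Where does the article leave choices to whoever analyses?**

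1. *Which measure leads.* Several measurements are called primary and none is singled out.
2. *Which readings count.* Item 1 gives three series of daily values (weight, blood pressure, blood sugar). The article does not say which days or averages form the start and end values.
3. *Which model is reported.* Stepwise and hierarchical regressions are both planned, so the choice and order of terms stay open.

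None of these requires knowing which arm is the app. With coded labels, the analyst can see that a choice changes the contrast but not which arm it helps.

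**Could the code be broken?** In part. In the app arm, "the Bluetooth wearable device automatically entered the values into the app". All women receive the devices, but how control readings are recorded is not described. If completeness differs between arms, the data pattern may suggest which is which.

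**The case against.** The strongest reply is that the sentence stands under a heading about allocation, next to one about the medical staff who register and assign. On that reading the word researchers means only those staff, and the reason is sound. The article also never says that the analyst is unmasked, and masking of analysts is often left to an analysis plan that is not shown. This has force: the text cannot be read as declaring every researcher open. What remains is that the noun is unqualified and nothing else in the article limits it. If only delivery staff were meant, the sentence should say so.

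Three stronger readings are tempting and are not supported:

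- *Bias is built in.* The article leaves open analysis permitted. It does not describe unmasked analysts choosing values, exclusions or models.
- *Birth records are extracted by unmasked staff.* No record extraction is described. For item 8 the advice can only be conditional.
- *The harm can be sized as 1 − 0.95^k.* This gives 1 − 0.95^5 = 23% for five independent null tests and 1 − 0.95^10 = 40% for ten. These are multiplicity rates. An analyst working with coded arms who picks the smallest p-value has the same rates, so they do not measure what coding would gain, and independence is doubtful for measures taken on the same women.

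It is also true that item 1 is measured by women who know their arm, and that much of the rest is questionnaires or checklists they complete. Masking the analyst leaves that bias untouched. The exploratory label lowers the stakes but does not supply a reason for open analysis.

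**Conclusion.** The point holds in limited form. The stated reason justifies openness for mothers and for enrolling, assigning and app-support staff. It does not justify it for the analysis of items 1 to 9, and the sentence does not separate these roles. The consequence is an avoidable opening for analyst bias in a plan with wide analytic freedom. It is neither a demonstrated bias nor a fatal flaw.

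Its size is not computable from the document. The conclusion assumes that the word researchers may include whoever analyses the data, since no exception is given, and that the choices listed above are not already fixed elsewhere. If a full plan already codes the arms, only the wording needs correction. The change is worth making as a low-cost improvement.

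**What to change.** - Under Allocation of participants, limit the statement to mothers and to enrolling, assigning and app-support staff.
- Under Statistical analysis, state that items 1 to 9 are analysed with arms coded X and Y, and that items 10 to 12 and usage logs are held in a separate file.
- Unmask only after the cleaning rules, the definition of start and end values for item 1, and the SPSS syntax are fixed.
- Where staff collect newborn data (item 8), do so without the arm field if feasible.

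The cost is a few sentences, one coded file prepared by someone other than the analyst, and a later merge of the app-only data. Masking may be incomplete if data patterns differ between arms. The Trial status section says that the trial has not started, so on that footing the change can precede any data. Multiplicity and self-report by unmasked mothers need separate handling.
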